**Figure 5 fig5:**
[figure not shown]
The procedure for splitting the training and testing sets for PD classification using ensemble learning.

A randomly sampled subset of the test set was used to predict with specialized models. This process was repeated five times for each combination of activity sets. The optimal combination of activity sets was selected based on each participant’s available recorded activities. Model outputs were then subjected to majority voting for the final classification as either PD or non-PD.

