##### Ensemble learning

2.3.2.3

The validation study dataset, as with many smartphone-based studies, contains missing data. Many participants only completed subsets of available tests, with less than half completing all available tests. In addition, PD symptoms are heterogeneous, meaning that patients can manifest different onset and progression patterns. To address these challenges, an ensemble classifier voting approach was employed. With this approach, the classifiers differ only in the training set based on the test activity, while the algorithm remains the same (creating a homogeneous ensemble).

Previous studies have demonstrated the benefits of accounting for the intersubject heterogeneity of PD by either combining the activity data or classifiers to enhance classification accuracy. Schwab and Karlen (145) introduced an evidence aggregation model (EAM) that integrates four trained NN models specialized in detecting PD for each test activity (walking, voice, finger tapping, and memory). This approach aims to combine several model outputs and generate a single diagnostic score. The EAM achieved an AUC of 0.85, surpassing the PD classification achieved by a single activity with single classifiers. Prince et al. (97) implemented a multi-source ensemble learning approach that utilizes three test activities (walking, voice, and finger tapping) with combined classifiers, including single neuron, random forest, convolutional NN, and deep NN. The ensemble approach classification accuracy was 82%, outperforming single activity with single or combined classifiers for PD classification. Therefore, an ensemble approach will be used for the Parkinson’s disease risk survey data analysis.

The procedure for splitting the training and testing sets for PD classification using ensemble learning is illustrated in Figure 5. Of the 343 people with PD, 162 completed all tests, while among the 230 individuals without PD, 128 completed all tests. Data from subjects who completed all tests (denoted as data t) were divided into a 90% training set and a 10% test set. The training set was combined with the data from subjects who did not complete all tests (denoted as data r) to train a specialized model for each test.

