**Figure 9 fig9:**
[figure not shown]
Receiver operating characteristic of classifiers using gait data (left) and balance data (right).

Overall, the AUC values of the specialized classifiers ranged from 0.82 to 0.88. Balance testing achieved the highest AUC of 0.88. The ensemble classifier, which utilized a combination of questionnaire responses, voice vowels, rest tremor, gait and balance activities achieved a PD prediction accuracy of 0.9108 (Table 7). Taken together, these results confirmed the validity of the selected digital markers and the mobile application and testing system for distinguishing between subjects with and without PD.

**Table 7 tab7:** The top eight test activity combination sets achieved the highest mean accuracies when evaluated on five randomly sampled test sets.

Activity count	Activities									Accuracy of 10-fold CV test set randomly selected 5 times	
	Questionnaire	Voice sentence	Voice vowel	Postural tremor	Rest tremor	Gait	Balance	Dual tap	Pinch-to-size	Mean	SD
5	✓		✓		✓	✓	✓			0.9108	0.012357
8	✓	✓	✓	✓	✓	✓	✓		✓	0.9106	0.006148
8	✓	✓	✓	✓		✓	✓	✓	✓	0.9094	0.011908
5	✓	✓	✓	✓			✓			0.9094	0.006285
8	✓		✓	✓	✓	✓	✓	✓	✓	0.9046	0.010918
7	✓		✓	✓	✓	✓	✓		✓	0.9042	0.009391
8	✓	✓		✓	✓	✓	✓	✓	✓	0.9032	0.013221
7	✓		✓	✓		✓	✓	✓	✓	0.9018	0.008849

Activity count indicates the number of specialized classifiers used for ensemble learning.CV, cross validation; SD, standard deviation.

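### The ensemble procedure as worded (random subsets of a 10% test set, at most about 29 people) did not produce Table 7, which labels the same accuracies as 10-fold cross-validation

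*Protocol article*

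**What the plan says.** All places are in the protocol article.

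- **Section 2.3.2.3, who is in the evaluation:** "Of the 343 people with PD, 162 completed all tests, while among the 230 individuals without PD, 128 completed all tests". That is 162 + 128 = 290 completers.
- **Section 2.3.2.3, the split:** "Data from subjects who completed all tests (denoted as data t) were divided into a 90% training set and a 10% test set". Non-completers are added to the training portion.
- **Section 2.3.2.3, text after Figure 5, the scoring:** "A randomly sampled subset of the test set was used to predict with specialized models. This process was repeated five times for each combination of" (test activities). The model outputs are combined by majority vote into one PD or non-PD class.
- **Section 2.3.2.5, Table 7, column heading:** "Accuracy of 10-fold CV test set randomly selected 5 times". The table title adds a third description, "when evaluated on five randomly sampled test sets".

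The ensemble section does not mention 10-fold cross-validation. Section 2.3.2.2 describes it for the single-activity classifiers. Table 7 does not state how many people lie behind its best accuracy, 0.9108, or what its SD is taken over.

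**The concern.** The methods text and the results table describe different evaluation sets for the same numbers. Read as written, the methods text scores each activity combination on at most about 29 people per run, drawn five times from one small pool. A 10-fold cross-validated test set would let all 290 completers be predicted.

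This matters because 0.9108 is the ensemble result offered as evidence that the markers and application are valid, and the article concludes that the platform is highly accurate. Section 2.3.2.3 also says that an ensemble approach will be used for the survey data, so its description serves as a method to follow. A reader cannot attach a precision to 0.9108 without knowing the number of people tested. Anyone who followed the wording literally would rank combinations on at most 29 people, although the eight listed combinations differ by less than one percentage point.

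**Working it through.** **Inputs.** Completers: 162 PD and 128 non-PD (section 2.3.2.3). Split 90/10 and five repeats (same section). Table 7 means run from 0.9108 down to 0.9018. Its SDs are 0.012357, 0.006148, 0.011908, 0.006285, 0.010918, 0.009391, 0.013221 and 0.008849.

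**Step 1: size of the test set.** 0.10 × (162 + 128) = 0.10 × 290 = 29 people. A subset of it has at most 29.

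**Step 2: smallest SD the worded procedure can give.** Assume each run yields one accuracy k/n, with people as the unit and the same n in every run. The smallest non-zero spread over five runs occurs when four runs agree and one differs by a single person, 1/n. The sum of squared deviations is then (1/n²) × (1 − 1/5) = 0.8/n².

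- Divisor 5: SD = √(0.8/5)/n = 0.4/n. At n = 29 this is 0.0138.
- Divisor 4: SD = √(0.8/4)/n = √0.2/n. At n = 29 this is 0.0154.

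Smaller subsets raise the minimum: at n = 20 it is √0.2/20 = 0.0224.

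**Step 3: compare with Table 7.** The largest printed SD is 0.013221 and the smallest is 0.006148. All eight are above zero and below 0.0138. To reach even the largest, n must be at least 0.4/0.013221 = 30.3, so 31 people (34 with divisor 4). To reach the smallest, n must be at least 0.4/0.006148 = 65.1, so 66 people (73 with divisor 4).

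**Step 4: the means.** With n = 29 the mean of five runs is a multiple of 1/145. The grid values nearest the printed means are 0.9034 and 0.9103, and no Table 7 mean equals either.

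**Step 5: relax the equal-size assumption.** All sets of five accuracies with subset size free to vary from 10 to 29 between runs were enumerated, with both SD divisors. No row was reproduced to the printed precision, with accuracies exact or rounded to three decimals. With a common size, no n from 5 to 59 reproduced any row.

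**Step 6: does 10-fold cross-validation over all completers fit?** With n = 290 the smallest non-zero SD (divisor 4) is √0.2/290 = 0.0015, so SDs of 0.006 to 0.013 are attainable in size. An exact match is not obtained. The mean of five pooled accuracies lies on a grid of 1/1450, whose neighbours of 0.9108 are 0.9103 and 0.9110. With accuracies rounded to three decimals, one of the eight rows is matched. Averaging over folds of unequal size could explain the remainder, but the article does not say that this was done.

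**Step 7: scale.** Binomial standard error at 0.91, √(0.91 × 0.09/n): 0.053 at n = 29 and 0.017 at n = 290. The spread across the eight rows is 0.9108 − 0.9018 = 0.0090, or 0.9 points. One person in 29 is 1/29 = 3.4 points.

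**The case against.** The best defence is that the 90/10 split is shorthand for one fold. The article does not say that the split was made once. Section 2.3.2.2 uses almost the same 90/10 description immediately after stating that 10-fold cross-validation was employed. Read that way, the split, the Table 7 heading and the Table 7 title can be reconciled, and the size of the SDs favours this reading. Figure 5, which illustrates the splitting procedure, is not available here and may show it. This defence stands as a plausible account of what was done. It does not rescue the text: predicting a random subset of the test set is not what 10-fold cross-validation does, and that sentence remains at odds with the table.

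The second objection is that the impossibility is conditional. It needs people as the unit and one accuracy per run. Averaging over folds within each run, or scoring recordings instead of people, would allow finer steps. That is correct, but the ensemble section describes neither: it splits subjects and takes a majority vote to one final class. The 0.0138 and 0.0154 limits also need equal subset sizes, although dropping that condition still reproduces no row.

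A reader might infer that 0.9108 itself rests on 29 people and so carries a standard error of about 5 points. The documents do not support that, because the same SDs that rule out the worded procedure also show that 0.9108 did not come from it.

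**Conclusion.** The point holds as a contradiction between the ensemble methods text and Table 7, confirmed by the table's own SDs. Assuming people are the unit and each run gives one accuracy, the procedure as worded did not produce Table 7. Its smallest possible non-zero SD at a common subset size is 0.0138, against a printed maximum of 0.0132, and varying the size from 10 to 29 does not help.

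A reader might also infer that 10-fold cross-validation over all 290 completers is now established as the method used. It is not: it fits the SDs in size but reproduces only one of the eight rows. What is known is that the number of people behind 0.9108 is unstated and that the written method is not its source. The two candidate readings differ ten-fold in people tested, hence about three-fold in standard error (5.3 against 1.7 points). Those figures show the range at stake; neither is an established standard error for the reported result.

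Under either reading, an SD over repeats on the same people understates the sampling uncertainty of the accuracy. The correction should be made, but it does not show that the reported accuracy is wrong.

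**What to change.** 1. Rewrite the split-and-score description in section 2.3.2.3, including the text after Figure 5, so that it states the scheme that actually produced Table 7. Make the Table 7 heading and title agree with it.
2. State in Table 7 the number of distinct people tested and what the SD is taken over (repeats, folds or something else).
3. If any hold-out or subset of the test set was used, recompute Table 7 by repeated participant-level 10-fold cross-validation over all 290 completers, with non-completers used in training only.
4. Report a confidence interval for the accuracy based on the number of distinct people tested, beside or in place of the SD over repeats.

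The cost is wording, or one re-run on existing data. The stated precision may become less favourable.

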##### Classification metrics

2.3.2.4

The performance of specialized and ensemble classifiers in distinguishing between PD and non-PD was assessed using the area under the receiver operating characteristic (ROC) curve (AUC) (146). The ROC curve illustrates the true positive rate and false positive rate at different classification thresholds, with PD assigned as the positive class and non-PD as the negative class. The true positive rate represents the ratio of correctly predicted PD cases to the total number of actual PD cases, while the false positive rate reflects the ratio of incorrectly predicted PD cases to the total number of actual non-PD cases. AUC calculations were performed using the “sklearn.metrics” function in Python’s scikit-learn library, version 1.3.0.

The true positive rate (TPR) and true negative rate (TNR) were calculated using Equations 1, 2 to demonstrate the proportion of correct predictions for each class by the ensemble classifiers.

(1)
$$TPR=\frac{TP}{TP+FN}\#$$

(2)
$$TNR=\frac{TN}{TN+FP}\#$$

Where 
TP
 (true positive) is the number of correctly PD cases, 
FN
 (false negative) is the number of PD cases incorrectly predicted as non-PD, 
TN
 (true negative) is the number of correctly predicted non-PD cases, and 
FP
 (false positive) is the number of non-PD cases incorrectly predicted as PD.

The accuracy, Equation 3, calculated as the number of correctly predicted PD cases divided by the total number of predictions, is as follows.

(3)
$$\mathrm{Accuracy}=\frac{TP+TN}{TP+TN+FP+FN}\#$$

The precision-recall (PR) curve was specifically used to compare PD classification when using voice vowel and voice sentences. This examination aimed to assess whether the data imbalance between PD and non-PD has an impact on classifier performance in this metric compared to the ROC curve (147). For instance, classifiers may predict PD accurately but perform poorly in predicting non-PD cases. The PR curve was calculated using the “sklearn.metrics” version 1.3.0.

##### Validation results

2.3.2.5

Table 6 summarizes PD classification performance using classifiers specialized for individual activity data, measured by the mean AUC with 10-fold cross validation. PD classification using balance data achieved the highest mean (±SD) AUC of 0.88 ± 0.06. The use of voice vowels resulted in a mean (±SD) AUC of 0.82 ± 0.04, which was the lowest value.

**Table 6 tab6:** Mean area under the receiver operating characteristic curve after 10-fold cross validation for each test activity.

Activity	Mean AUC ± SD
Balance	0.88 ± 0.06
Postural tremor	0.87 ± 0.06
Dual tapping	0.86 ± 0.05
Pinch-to-size	0.85 ± 0.05
Gait	0.84 ± 0.07
Questionnaire	0.83 ± 0.04
Voice sentences	0.83 ± 0.04
Rest tremor	0.83 ± 0.06
Voice vowel	0.82 ± 0.04

Test activities are sorted by their mean area under the curve (AUC) in descending order.SD, standard deviation.

Using voice vowel and voice sentence data ROC curves for PD classification using RF with 10-fold cross validation showed mean (±SD) AUC values of 0.82 ± 0.04 and 0.83 ± 0.04, respectively (Figure 6). Using resting tremor data and postural tremor data, ROC curves for PD classification using RF with 10-fold cross validation showed mean (±SD) AUC values of 0.83 ± 0.06 and 0.87 ± 0.06, respectively (Figure 7). Using dual tapping and pinch-to-size data, ROC curves for PD classification using RF with 10-fold cross validation showed mean (±SD) AUC values of 0.86 ± 0.05 and 0.85 ± 0.05, respectively (Figure 8). Using gait and balance data, ROC curves for PD classification using RF with 10-fold cross validation showed mean (±SD) AUC values of 0.84 ± 0.07 and 0.88 ± 0.06, respectively (Figure 9).

**Figure 6 fig6:**
[figure not shown]
Receiver operating characteristic curve of classifiers using voice vowel data (left) and voice sentence data (right).

**Figure 7 fig7:**
[figure not shown]
Receiver operating characteristic curve of classifiers using rest tremor data (left) and postural tremor data (right).

**Figure 8 fig8:**
[figure not shown]
Receiver operating characteristic of classifiers using alternate finger tapping data (left) and pinch-to-size data (right).

**Figure 9 fig9:**
[figure not shown]
Receiver operating characteristic of classifiers using gait data (left) and balance data (right).

Overall, the AUC values of the specialized classifiers ranged from 0.82 to 0.88. Balance testing achieved the highest AUC of 0.88. The ensemble classifier, which utilized a combination of questionnaire responses, voice vowels, rest tremor, gait and balance activities achieved a PD prediction accuracy of 0.9108 (Table 7). Taken together, these results confirmed the validity of the selected digital markers and the mobile application and testing system for distinguishing between subjects with and without PD.

**Table 7 tab7:** The top eight test activity combination sets achieved the highest mean accuracies when evaluated on five randomly sampled test sets.

Activity count	Activities									Accuracy of 10-fold CV test set randomly selected 5 times	
	Questionnaire	Voice sentence	Voice vowel	Postural tremor	Rest tremor	Gait	Balance	Dual tap	Pinch-to-size	Mean	SD
5	✓		✓		✓	✓	✓			0.9108	0.012357
8	✓	✓	✓	✓	✓	✓	✓		✓	0.9106	0.006148
8	✓	✓	✓	✓		✓	✓	✓	✓	0.9094	0.011908
5	✓	✓	✓	✓			✓			0.9094	0.006285
8	✓		✓	✓	✓	✓	✓	✓	✓	0.9046	0.010918
7	✓		✓	✓	✓	✓	✓		✓	0.9042	0.009391
8	✓	✓		✓	✓	✓	✓	✓	✓	0.9032	0.013221
7	✓		✓	✓		✓	✓	✓	✓	0.9018	0.008849

Activity count indicates the number of specialized classifiers used for ensemble learning.CV, cross validation; SD, standard deviation.

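### The headline ensemble accuracy of 0.9108 is the best of an unstated number of combinations, ranked and reported on the same test data, so it is somewhat optimistic, and the SD beside it is not its precision

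*Protocol article*

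**What the plan says.** Section 2.3.2.3 (Ensemble learning) defines the people available for testing: "Of the 343 people with PD, 162 completed all tests, while among the 230 individuals without PD, 128 completed all tests". Those who completed everything are split 90% to 10%. The training part is pooled with the incomplete participants to train one classifier per test, and random subsets of the test part are then scored by majority vote. On repetition it says: "This process was repeated five times for each combination of activity sets". On the choice of combination it says: "The optimal combination of activity sets was selected based on each" participant's available recordings.

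Section 2.3.2.5 (Validation results) then reports: "The ensemble classifier, which utilized a combination of questionnaire responses, voice vowels, rest tremor, gait and balance activities achieved a PD prediction accuracy of 0.9108". That is row 1 of Table 7, captioned "The top eight test activity combination sets achieved the highest mean accuracies when evaluated on five randomly sampled test sets". The column that holds the mean and SD is headed "Accuracy of 10-fold CV test set randomly selected 5 times". The next sentence of the text takes the results together as confirming the validity of the markers and of the system.

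**The concern.** When many candidates are scored with error on one set of people and the highest score is reported, that score is too high on average. It contains the winner's luck as well as its merit. An unbiased figure needs participants who played no part in the ranking, and the text describes none: no inner folds, no selection set and no external sample.

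Two further points follow. An SD over repeated selections from one cohort shows how much the result moves when the split changes. It does not show how much it would move with a different 290 people, yet it is the only measure of spread given. The table also invites the reader to prefer the five-test set in row 1, although its margin over the other rows is very small.

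The figure matters because it is the paper's only accuracy statement for the combined tool, and national roll-out is already under way.

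**Working it through.** **Inputs from the article.** Headline accuracy 0.9108, SD 0.012357 (Table 7, row 1). SDs over the eight rows: 0.006148 to 0.013221. Row 2: 0.9106. Row 8: 0.9018. Complete-test participants: 162 + 128 = 290. Inputs: eight digital markers plus the questionnaire, so nine (Tables 6 and 7). Single-test AUCs: 0.82 to 0.88 (Table 6).

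**The plan's own figure.** The accuracy in the text matches row 1 of Table 7. The five repeat values and the individual predictions are not published, so neither the mean nor the SD can be recomputed.

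**Number of candidates.** Non-empty subsets of nine inputs: 2^9 − 1 = 511. This is an upper bound; requiring at least three tests leaves 466. The article does not say how many were tried.

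**Sampling error.** If each repeat of the ten-fold scheme covers all 290 people, SE = √(0.9108 × 0.0892 / 290) = 0.0167. The Wilson 95% CI is 0.872 to 0.938, with no correction for selection. Against the headline SD this is 0.0167 / 0.0124 = 1.35 times larger. Over the eight rows the ratio is 1.3 to 2.7.

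**Size of the selection effect, simple model.** For K equally good combinations with pairwise correlation r between their accuracy estimates, the expected excess of the best is m(K) × SE × √(1 − r). Here m(K) is the expected maximum of K standard normal values: m(511) = 3.04, m(100) = 2.50. With SE = 0.0167:

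| K | r = 0.80 | r = 0.90 | r = 0.95 |
|---|---|---|---|
| 511 | 0.023 | 0.016 | 0.011 |
| 100 | 0.019 | 0.013 | 0.009 |

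**Size of the selection effect, simulation.** Nine normally distributed scores were given the Table 6 AUCs and a common within-group correlation. All 511 majority votes were scored on 162 PD and 128 non-PD participants, and the best was picked on the same people. An apparent best near 0.91 arises only with a correlation of about 0.15 to 0.2. In those settings the optimism was about 0.009 to 0.025, and the lower values occur when part of the noise is redrawn over five repeats. Over all settings tried it was about 0.009 to 0.034. At correlations of 0.4 and 0.6 the apparent best was only about 0.87 and 0.84, so those settings do not describe this study.

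Rounded, the optimism is 0.01 to 0.03: 0.9108 − 0.03 = 0.88 and 0.9108 − 0.01 = 0.90.

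**The ranking.** Rows 1 and 8: 0.9108 − 0.9018 = 0.0090, and 0.0090 × 290 = 2.6 people. Rows 1 and 2: 0.0002 × 290 = 0.06 of a person. The combinations are scored on the same people, so the comparison is paired. With each person counted once, the case most favourable to a real difference is that the two sets disagree on 0.009 of people, all in one direction. Then SE = √((0.009 − 0.009²) / 290) = 0.0055 and z = 0.0090 / 0.0055 = 1.6. More disagreement lowers z. Averaging each person's result over repeats could change this, but the paired data needed to check are not given.

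**The case against.** Several points on the other side stand.

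- A reader might infer that the true accuracy is 0.88. That is the pessimistic end of a range that depends on an assumed correlation and on up to 511 candidates, neither of which the article states.
- A reader might take one 10% split of 29 people and quote SE = √(0.9108 × 0.0892 / 29) = 0.053. The table does not support this. Separate 29-person draws would give an SD near 0.05, not 0.006 to 0.013, and the column heading refers to ten-fold cross-validation. The 290-person figure is the reasonable one.
- A reader might say that the error bars are wrong. The column is labelled as an SD over five selections, and no confidence interval is claimed. The fault arises only if the SD is read as precision, and for row 1 the shortfall is modest.
- A reader might say that the accuracy ranking decides which tests vote. Section 2.3.2.3 gives a different rule, availability of each participant's recordings. The two statements need reconciling; the text does not establish that the ranking drives the vote.
- A reader might say that the validity claim falls with 0.9108. It is drawn from all the results together, including single-test AUCs that were not picked from combinations. Four of the eight rows are eight-test sets at 0.9032 to 0.9106, so good performance does not hinge on the winning set.

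Figure 5, which illustrates the split, could not be read for this check. If it shows separate selection data, the bias argument falls and a request for clearer reporting remains. None of the other points removes the bias: the reported figure is still the maximum on the data that ranked it.

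**Conclusion.** The point holds in a moderate form. As described in the text, 0.9108 is selected and reported on the same test data, so it is optimistic by roughly 0.01 to 0.03, and an accuracy of about 0.88 to 0.90 is more plausible. The direction follows from the described procedure. The size rests on the assumed correlation between tests, the assumed number of combinations and the assumption that each repeat covers all 290 people.

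The printed SD should not be read as precision, since participant sampling alone gives a standard error of about 0.017. Table 7 does not show that any of its eight combinations is better than another. This should be fixed, but it is not fatal: an accuracy of 0.88 to 0.90 with single-test AUCs of 0.82 to 0.88 would still show that the tool separates the two groups in this cohort.

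**What to change.** 1. Choose the combination in the inner folds of a nested cross-validation, split by participant, and report accuracy, TPR and TNR from the outer folds. Section 2.3.2.4 defines TPR and TNR, but Table 7 gives accuracy only. Alternatively, fix in advance the ensemble that uses every available test and report that. No nine-input row is among the eight in Table 7; if that set was tried, its mean was no higher than 0.9018.
2. Give a 95% CI from a bootstrap that resamples participants. Keep the SD over five selections only as a measure of split-to-split variation, and label it so.
3. Give paired CIs for differences between combinations, or drop the ranking.
4. State how many combinations were tried.
5. Reconcile the availability-based rule in section 2.3.2.3 with the accuracy ranking in Table 7, and say which one the survey will use.

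Until this is done, describe 0.9108 as the highest of the combinations tried, uncorrected for selection. The cost is computing time on existing data, a slightly lower headline accuracy and a wider interval.
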